### Procedure

At the beginning of the session, we will reassess participants' eligibility, and we will collect their informed consent. We will also collect data relating to our independent variables, using a series of questionnaires, physiological measures, and a blood sample. All questionnaires will be provided in each participant's preferred language (English or French). We will then assess the amplitude of their CPM and TS using quantitative sensory testing (Figure 1):

**Figure 1 F1:**
[figure not shown]
Illustration representing the sequence of the experimental procedure.

#### Thermode Calibration

Pre-tests will be conducted using an experimental thermode (9 cm^2^, TSA II), at a temperature increasing from 32° to 51°C at a rate of 0.3°C/s. Participants will be asked to identify the point at which heat becomes painful (heat pain threshold) and the point at which it becomes intolerably painful (heat pain tolerance).

One pre-tests will be conducted on the left hand of each participant, so they become familiar with the thermode and CoVAS. Three more pre-tests will be conducted on the anterior side of the left forearm, to identify the average temperature eliciting a pain intensity of 50/100. This temperature will be used as the Heat Test Stimulus (see below).

#### Pre-CS Test Stimuli

Two Pre-CS Test Stimuli will be used in our study: a painful mechanical pressure and a painful heat stimulus. The Mechanical Test Stimulus will be administrated using the digital algometer, applied on the upper trapezius muscle at the mechanical pain threshold (see *Independent Variables—Mechanical pain*). The average pressure required to reach the mechanical pain threshold before and after the CS will be compared to assess CPM.

The second Test Stimulus will consist of a 2 min heat pain stimulation, delivered by the thermode applied on the left forearm of participants, at an individually tailored temperature selected to evoke pain levels of 50/100 (based on the pre-tests). Although the thermode temperature will be kept constant during the stimulation (following a gradual increase from 32°C to the target temperature, at a rate of 0.3°C/s), participants will be told that the temperature will randomly vary (increase, remain stable, or decrease). Participants will be asked to rate their pain during the stimulation using the CoVAS. This Heat Test Stimulus will serve two purposes: first, like the Mechanical Test Stimulus, it will be used as a pre- and post-CS comparator to assess CPM; second, it will be used to evaluate TS, which will be measured as the change in pain levels throughout the heat test stimulation.

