##### Mechanical Pain Threshold

A digital algometer will be used to assess the mechanical pain threshold (i.e., the point at which a mechanical pressure starts to elicit pain). The algometer will be placed on the upper trapezius muscle, and the pressure will be gradually increased until the participant verbally reports pain. Four trials will be conducted—two on each side—and the average pressure required to reach the mechanical pain threshold will be recorded. This test has good to excellent reliability and validity (80–82).

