#### Post-CS Test Stimuli

The Heat Test Stimulus will be administered again immediately after the CS, using the same parameters as for the pre-CS stimulation. Following this, the Mechanical Test Stimulus will also be re-administered; again, four trials will be conducted and the average pressure corresponding to the pain threshold will be recorded. Comparisons between pre-CS and post-CS scores will be used to assess CPM.

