### TS and CPM Amplitude

The amplitude of TS (*A*_*TS*_) will be measured as the difference in pain intensity elicited by the thermode during the heat test stimulation (first instance the Heat Test Stimulus). We will subtract the pain level at 0 s (time the thermode reaches the target temperature) from the pain level at 120 s, so that a positive score represents an increase in pain level. The amplitude of CPM (*A*_*CPM*_) will be measured as the difference in pain level elicited by the thermode (calculated as the average of all pain scores taken throughout the 2 min test stimulation) before and after the cold water bath, and as the difference in pressure required to reach mechanical pain threshold before and after the cold water bath.

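### If mechanical CPM is modelled, the pre-conditioning pain threshold is apparently both a candidate predictor and the outcome's baseline term, so shared measurement error modestly flatters the prediction

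*Protocol article*

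**What the plan says.** All references are to the protocol article.

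- **Predictor.** Mechanical Pain Threshold, within Independent Variables: "Four trials will be conducted—two on each side—and the average pressure required to reach the mechanical pain threshold will be recorded".
- **Pre-conditioning comparator.** Pre-CS Test Stimuli describes the mechanical test stimulus as "applied on the upper trapezius muscle at the mechanical pain threshold (see *Independent Variables—Mechanical pain", a pointer back to the predictor, and continues: "The average pressure required to reach the mechanical pain threshold before and after the CS will be compared to assess CPM".
- **Post-conditioning comparator.** Post-CS Test Stimuli: "again, four trials will be conducted and the average pressure corresponding to the pain threshold will be recorded".
- **Outcome.** TS and CPM Amplitude gives CPM two definitions. The heat version "will be measured as the difference in pain level elicited by the thermode" before and after the cold water bath. The mechanical version is defined "as the difference in pressure required to reach mechanical pain threshold before and after the cold water bath".
- **Analysis.** Statistical Analyses plans one model per mechanism. A lasso on the discovery cohort selects the predictors, with the penalty that minimises leave-one-out prediction error. The model is then judged by mean square prediction error in a healthy and a chronic pain validation cohort. The section does not say which CPM measure is the outcome, and it mentions no special handling of the threshold.

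**The concern.** The outcome is post minus pre, and pre is also offered as a predictor. Any error in the pre-conditioning reading raises the predictor and lowers the outcome by the same amount. This is mathematical coupling: a negative association appears even if a person's true threshold says nothing about true inhibition.

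The new participants in the validation cohorts give no protection. They go through the same procedure, so the same shared error is in their data and the false part of the prediction replicates.

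The Discussion wants an equation into which a clinician enters simple test results to estimate a patient's CPM. An algometer reading taken in clinic shares no error with that patient's CPM, so the part of the apparent accuracy that comes from coupling would not carry over.

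**Working it through.** **Inputs from the article.** Discovery cohort n = 360, smallest expected R² = 0.4, 24 predictors, shrinkage at least 0.9 (Sample Size). Four trials before and four after conditioning.

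**Assumptions.** The same four pre-conditioning trials serve as predictor and baseline. The article rates the reliability of the threshold favourably but gives no figure, so reliability r is taken over 0.7 to 0.95.

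**The plan's own figure.** n = p(1 − R²)/[R²(1 − S)] = 24 × 0.6/(0.4 × 0.1) = 360. It reproduces, and this point does not affect it.

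**Step 1: the coupling.** Let pre X = T + e1 and post Y = T + D + e2, with var(X) = 1, each error variance 1 − r, and true change D independent of T with variance d. Then

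- Y − X = D + e2 − e1, with variance d + 2(1 − r);
- cov(X, Y − X) = −(1 − r);
- artefactual R² = (1 − r)²/[2(1 − r) + d].

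**Step 2: the ceiling.** With d = 0 this is (1 − r)/2. But d = 0 means that true CPM does not differ between people. The outcome is then pure measurement error and no genuine predictor could explain any of it.

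**Step 3: a size consistent with the plan.** If genuine predictors explain 0.4 of the variance of Y − X, true change must supply at least that share: d ≥ 0.4[d + 2(1 − r)], so d ≥ 1.33(1 − r). The denominator is then at least 3.33(1 − r), and the artefactual R² is at most 0.3(1 − r).

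| Assumed r | Ceiling, d = 0 | At most, if genuine R² = 0.4 | Second figure as share of 0.4 |
|---|---|---|---|
| 0.95 | 0.025 | 0.015 | 3.75% |
| 0.9 | 0.05 | 0.03 | 7.5% |
| 0.8 | 0.10 | 0.06 | 15% |
| 0.7 | 0.15 | 0.09 | 22.5% |

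**Step 4: effect on prediction error.** If the genuine predictors are uncorrelated with the threshold, they leave 0.6 of the outcome variance unexplained. The artefact lowers this to at best 0.6 − 0.03 = 0.57 at r = 0.9 (5% lower) and 0.6 − 0.09 = 0.51 at r = 0.7 (15% lower).

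**Step 5: selection.** The planned lasso, tuned by leave-one-out error, was simulated with n = 360 and 24 candidates, 60 runs per row. True CPM was unrelated to the true threshold throughout. In the first two columns, genuine R² is the share explained by five other candidates, and extra variance is true change that no candidate explains, as a fraction of var(X).

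| Genuine R² | Extra variance | r | Threshold kept | Pure-noise candidates kept |
|---|---|---|---|---|
| 0 | 0 | 0.8 | 100% | 20% |
| 0 | 0 | 0.9 | 100% | 18% |
| 0 | 0 | 0.95 | 92% | 14% |
| 0.4 | 0.1 | 0.8 | 100% | 38% |
| 0.4 | 0.1 | 0.9 | 98% | 41% |
| 0.4 | 0.3 | 0.9 | 95% | 39% |
| 0.4 | 0.1 | 0.95 | 88% | 39% |

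The mean coefficient was negative in every row.

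**Step 6: check on the cause.** When the predictor was a separate pre-conditioning measurement with its own error (r = 0.9), it was kept in 10% of runs with no genuine predictors (noise candidates 11%) and in 35% with genuine R² = 0.4 and extra variance 0.1 (noise candidates 37%). The shared error drives the selection.

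**The case against.** **The candidate list and the outcome are not fully stated.** The article does not name the 24 predictors or say that the threshold enters a mechanical-CPM model, and outcome-specific lists are ordinary detail for an analysis plan. If only heat CPM is modelled, the problem does not arise. This stands, and it makes the point conditional. It does not remove it: the article classes the threshold as an independent variable, builds one CPM measure from it, and limits neither use.

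**The two readings might be separate.** Procedure collects the independent variables first, Pre-CS Test Stimuli describes the mechanical stimulus as a step of its own, and the sequence figure is not available here. Separate readings would remove the artefact (step 6). The cross-reference, and the absence of any second set of pre-conditioning trials, favour a single reading, but the article does not say so outright.

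**A predictor that works is legitimate.** This would hold if the equation were to be used on readings that also form the outcome. It is meant for clinic readings that do not.

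**Selection means little under this lasso.** With genuine predictors present, noise candidates were kept in 38–41% of runs, so being kept is weak evidence of anything. That is fair, and the coefficient is small. The harm is a modest, systematic flattering of prediction error that validation cannot detect.

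**Conclusion.** The point stands for mechanical CPM only, provided that mechanical CPM is modelled and the same four trials fill both roles. The threshold will then very likely be kept even if true CPM is unrelated to baseline, and both validation cohorts will repeat the artefact. If genuine predictors reach R² = 0.4, the artefact adds at most 0.015 to 0.09, depending on a reliability that the article does not give. TS and heat CPM do not contain the threshold.

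Three stronger readings are tempting, and the article does not support them:

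- **That an eighth to over a third of the planned R² is artefact** (0.05/0.4 = 12.5%; 0.15/0.4 = 37.5%). The range 0.05–0.15 requires that true CPM does not vary between people, which cannot be combined with a genuine R² of 0.4.
- **That selection is certain.** It was 88–100% in simulation under assumed reliabilities, and lowest at 0.95.
- **That a reported R², or a claim that one algometer reading stands in for CPM, would be spurious.** R² appears only in the sample-size assumption, the stated criterion is mean square prediction error, and the article describes an equation of several variables.

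**What to change.** State which CPM measure or measures are modelled, and whether the listed threshold and the pre-conditioning comparator are the same four trials. Then, for the mechanical-CPM model, choose one of these:

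1. Exclude the mechanical pain threshold from the lasso candidates.
2. Model the post-conditioning threshold with the pre-conditioning threshold forced in unpenalised. Report the reduction in prediction error beyond that baseline-only model, in the discovery cohort and in both validation cohorts.

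Keep the threshold as a candidate for TS and heat CPM.

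The cost is about a sentence in Statistical Analyses, with no new participants or measurements. Apparent accuracy for mechanical CPM becomes slightly less favourable. Under the first option, any genuine link between baseline threshold and CPM is also given up, although the present design could not separate such a link from the artefact.

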#### Conditioning Stimulus (CS)

The conditioning stimulus, which serves to trigger CPM, will consist of the Cold Pressor Test, wherein participants immerse their right arm (up above the elbow) in a painfully cold water bath [10°C; (44)] for 2 min. This technique has been shown to consistently elicit CPM (92).

#### Post-CS Test Stimuli

The Heat Test Stimulus will be administered again immediately after the CS, using the same parameters as for the pre-CS stimulation. Following this, the Mechanical Test Stimulus will also be re-administered; again, four trials will be conducted and the average pressure corresponding to the pain threshold will be recorded. Comparisons between pre-CS and post-CS scores will be used to assess CPM.

## Ethical Aspects

This study will be conducted in accordance with the Helsinki Declaration and the International Council for Harmonization of Good Clinical Practices. Participants will be informed of the purpose and process of this study. We will collect their written informed consent, reminding them that participation in this study is purely voluntary and that they can withdraw at any time without negative repercussions, and we will preserve the confidentiality of their data. Participants will be asked to skip only the dose of their analgesic medication immediately preceding the experimental session, to minimize undue pain. The trial is registered at clinicaltrial.gov (NCT03376867).

## Statistical Considerations

### Sample Size

It is customary in predictive analysis to use a rule of thumb to calculate the sample size, wherein the number of subjects required for a multiple regression analysis is *n* = 10–15 subjects per variable (93). However, this rule often yields fitted models with limited predictive capabilities (94–98); as such, it is recommended that two cohorts be used: a discovery cohort, and a validation cohort—which, as their names suggest, are used to build the predictive model and to validate it, respectively (99).

We calculated a sample size of 360 participants for the discovery cohort, based on the smallest expected R^2^ (0.4) and the highest expected number of predictors (24) required to obtain a shrinkage coefficient (100) of at least 0.9 (101). The discovery cohort will be representative of the overall population, such that it will be comprised of 85% (*n* = 306) of healthy participants and 15% (*n* = 54) of patients suffering from chronic pain (102). The external validation cohort will be comprised of 54 (new) participants, corresponding to 15% of the size of the discovery cohort (103). We will use two such validation cohorts (*n* = 54 for both) in order to validate our model using both healthy participants and patients suffering from chronic pain. As such, a total of 468 participants will be recruited (360 healthy participants, and 108 patients suffering from chronic pain).

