##### Anxiety and Depression

The *Hospital Anxiety and Depression Scale* is an instrument used to screen for anxiety and depressive disorders. It comprises 14 items (seven each for anxiety and depression) rated from 0 to 3, for a maximum score of 21. Subjects are classified as presenting no symptoms (≤7), mild symptoms (8–10), or moderate to severe symptoms (≥11) for both disorders. The psychometric properties of this questionnaire are qualified as excellent (70).

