##### Blood Concentration

**Catecholamines** (53) (adrenaline, noradrenaline, dopamine, serotonin, and their metabolites), **Endocannabinoids** (anandamide, N-olcoylethanilamine, palmitoylethanolamine), and **Peptides** (83, 84) (Leu-Enképhaline, B-Endorphin, Dynorphine A, Substance P). Blood samples will be collected in K2-EDTA tubes and will be placed directly on ice. After centrifugation (4°C, 1,500 g, 15 min), samples will be directly stored at −80°C before analysis. The different analytes will be separated and analyzed by liquid chromatography coupled to a tandem mass spectrometer. The analysis will be carried out at the bioanalysis platform of the Sherbrooke Pharmacology Institute.

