This study will further our understanding of modulatory mechanisms and their relationship with a complex system of physiological, psychological and socio-demographic correlates, which will allow us to develop a predictive model to compute the pain modulation profile of individual patients based on their biopsychosocial characteristics. This model will consist in a simple equation in which clinicians can input the value of selected variables (obtained via simple clinical tests), in order to yield the predictive amplitude of their patients' CPM and/or TS response. The overarching goal of this study is to provide clinicians with a set of quick and cheap tests, easily applicable in day-to-day practice, in order to identify markers of pain modulation profiles and in turn orient pharmacological treatment, which will ultimately provide patients with a more hopeful outlook on their future and will lead to a more optimal use of ever limited health care resources. This protocol is the first step toward the development of a validated clinical tool.

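### The lasso may build the clinical equation from research-platform blood assays, and the 24 predictors behind n = 360 are the minimum count of the listed measures, with no slack

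*Protocol article*

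**What the plan says.** **Purpose.** The Introduction argues that present testing of these mechanisms is too slow, costly and complex for routine care, and that clinicians need an estimate from readily available tests. The Discussion describes the product: "This model will consist in a simple equation in which clinicians can input the value of selected variables (obtained via simple clinical tests"), and adds that the tests should be quick and cheap.

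**Candidates.** The Independent Variables section covers questionnaires, a pain diary for chronic pain participants, two algometer measures, blood pressure at three times, and blood analytes. The first analyte group is "adrenaline, noradrenaline, dopamine, serotonin, and their metabolites". Three endocannabinoids and four peptides follow. On method: "The different analytes will be separated and analyzed by liquid chromatography coupled to a tandem mass spectrometer", at a bioanalysis platform of a pharmacology institute. The Abstract adds sociodemographic characteristics without listing them.

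**Selection.** Under Statistical Analyses, a lasso on the discovery cohort chooses the variables for each mechanism. Its penalty minimises the leave-one-out estimate of mean square prediction error. No restriction to measures available in clinic is stated.

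**Size.** The Sample Size section sets the discovery cohort at 360. One input is an R² of 0.4, given as the lowest value anticipated. The other is a predictor count, introduced as "the highest expected number of predictors (24) required to obtain a shrinkage coefficient (100) of at least 0.9 (101"). The 24 are not enumerated.

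**The concern.** There are two linked problems.

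First, the candidate set and the selection rule do not serve the stated product. The lasso judges a variable only by what it adds to cross-validated prediction. If an assay helps, it stays, and the two validation cohorts then test an equation that needs it. A clinician without that value cannot simply omit the term, because the other coefficients were estimated with it in the model. The study could finish with a validated equation and none for the setting it was meant for.

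Second, the shrinkage target is the plan's own reason for 360. Expected shrinkage depends on the number of parameters screened, not the number retained. If 24 is the smallest count of the listed measures rather than the largest, any finer coding takes the plan below its target of 0.9.

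**Working it through.** **1. Reproduce 360.** Inputs from Sample Size: R² = 0.4, p = 24, target shrinkage S = 0.9. The article does not print its formula, so two common forms were tried. With (1 − R²)/R² = 0.6/0.4 = 1.5:

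- Simplified, n = p(1 − R²)/[R²(1 − S)] = 24 × 1.5/0.1 = 360 exactly. This also equals 15 subjects per variable × 24, the top of the rule of thumb the section cites.
- Copas-type, S = 1 − (p − 2)(1 − R²)/[R²(n − p − 1)]. At n = 360 and p = 24, S = 1 − 33/335 = 0.901; n = 355 would suffice.

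The stated figure therefore stands for p = 24.

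**2. Count the listed measures as sparingly as possible.**

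| Measure | Count |
|---|---|
| Age, sex (assumed; no list given) | 2 |
| Anxiety, depression | 2 |
| Catastrophizing | 1 |
| Brief Pain Inventory: intensity, interference | 2 |
| Neuropathic pain score | 1 |
| Diary, reduced to one number | 1 |
| Somatization | 1 |
| Mechanical threshold | 1 |
| Pain persistence | 1 |
| Blood pressure, reduced to one number | 1 |
| Named amines | 4 |
| Endocannabinoids | 3 |
| Peptides | 4 |
| **Total** | **24** |

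No metabolite is in this total, although the Blood Concentration section says metabolites will be measured. The blood analytes make up 4 + 3 + 4 = 11 of the 24.

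**3. Sensitivity to the count** (R² = 0.4):

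| p | Copas-type S at n = 360 | n for S = 0.9 |
|---|---|---|
| 24 | 1 − 33/335 = 0.901 | 355 |
| 25 | 1 − 34.5/334 = 0.897 | 371 |
| 28 | 1 − 39/331 = 0.882 | 419 |
| 35 | 1 − 49.5/324 = 0.847 | 531 |

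The simplified form gives 0.900, 0.896, 0.883 and 0.854. Under both, 24 is the largest p that holds 0.9 at n = 360. Assumptions: 28 adds one metabolite per amine to the 24. To reach 35, add five for blood pressure (systolic and diastolic at three times instead of one number) and two for the diary (three levels instead of one).

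**4. A clinic-available list.** Remove the 11 analytes and the diary: 24 − 11 − 1 = 12, or 13 if resting systolic and diastolic pressure enter separately. R² may be lower without the assays, so a range is needed (n = 360, Copas-type):

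| R² | p = 12 | p = 13 |
|---|---|---|
| 0.40 | 0.957 | 0.952 |
| 0.30 | 0.933 | 0.926 |
| 0.25 | 0.914 | 0.905 |
| 0.20 | 0.885 | 0.873 |

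For example, p = 12 and R² = 0.30 gives 1 − 10 × (0.7/0.3)/347 = 0.933. The target holds down to an R² of about 0.25. These R² values below 0.4 are illustrative and not from the article.

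**The case against.** The article lists instruments and assays, not coded parameters, and coding can be left to a fuller document. Another coding also gives 24 with metabolites kept: leave out the diary, the neuropathic score and the two Brief Pain Inventory scores as patient-oriented (24 − 4 = 20), then add one metabolite per amine (+4). A reader might infer that the true count is 28 to 35 and that 360 is therefore wrong. The documents do not support this, since the higher counts rest on coding the article never states. The objection stands to that extent. It does not explain why a number called the highest expected equals the sparest count of the list.

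The shrinkage formulas describe unpenalised regression on all candidates. The planned lasso applies its own shrinkage, and new participants then test the model. This stands too: the figures are a planning benchmark, not a forecast of the final model. They are nevertheless the benchmark the plan chose to justify its size.

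On purpose, the lasso may drop every assay. The main objective is worded as identifying predictors, the Introduction gives reasons to study the biomarkers, and the Discussion calls this a first step. A reader might infer that no clinic could run the assays or that the model will be unusable. The article says only that a research platform does them, so a misfit with the stated use is a risk, not a consequence. Measuring the biomarkers is reasonable. What is missing is any rule separating what they teach from what the clinical equation may contain.

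**Conclusion.** The point holds in two parts of unequal weight.

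The main part is the conflict between purpose and method. It rests on the documents alone and does not depend on the exact count: at least 11 candidates come from mass-spectrometry assays, nothing keeps them out of the selected model, and that model is meant to run on simple clinical tests.

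The lesser part is the predictor count. The arithmetic behind 360 is sound, and at least two codings give 24. However, 24 is the minimum that retains every listed measure without metabolites, and it assumes only two sociodemographic variables. One more parameter gives about 0.897 and four more about 0.88, at R² = 0.4. That is a small shortfall against 0.9 and no reason to enlarge the study, but the stated target has no margin and the list it applies to should be shown.

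**What to change.** 1. For each outcome, prespecify a lasso on a fixed list of clinic-available predictors recorded in all participants: age, sex, the questionnaires, the algometer measures and resting blood pressure. Leave out the diary, which only chronic pain participants complete and which would be missing for the 306 healthy participants in the discovery cohort. Confirm that the Brief Pain Inventory and neuropathic score are also recorded in healthy participants before listing them.
2. Name this the model for clinical use and validate it in both the healthy and the chronic pain validation cohorts.
3. Report the biomarker-extended lasso beside it, with the change in validated prediction error in each cohort. That shows what the assays add.
4. List the candidates of each model as coded, including the number of metabolites and of blood pressure and sociodemographic terms. Reconcile each count with 24 and state the expected shrinkage for it over a range of R². Keep n at 360.

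The cost is one more lasso per outcome and a short addition to the sample-size text, with no new data or participants. The clinical model may have a lower R² than the extended one.
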